For the adolescent cohort, assuming a baseline sustainable-product usage rate of 5% and a projected postintervention uptake of 20%, with 80% power and 5% significance, the minimum required sample size was calculated as 304 adolescent girls per site using a standard formula for comparing 2-proportions formula. To account for clustering by school and community catchment, a design effect of 1.5 (based on an assumed intracluster correlation coefficient of 0.02 and an average cluster size of 25 girls, consistent with design effects reported in comparable school-based menstrual health cluster studies) was applied, giving a minimum requirement of 456 adolescent girls per site (total N=912) for the phase 2 sensitization cohort. Of these, a subgroup of 416 girls (n=208 per site) will be enrolled in the phase 3 product-use follow-up; this subgroup size was determined pragmatically in line with recommendations for feasibility and pilot studies, which emphasize that a fully powered comparative sample is not required at this stage but that sample size should still be justified in relation to the primary feasibility objectives (recruitment, retention, and product continuation) rather than a hypothesis-testing end point [22,23]. A minimum of 30‐35 participants per arm per site is considered adequate to estimate continuation and acceptability proportions with reasonable precision (95% CI width ≤±16%) for feasibility purposes, and the planned 203 girls per site substantially exceeds this threshold, allowing additional precision for the secondary comparison between MC and MP users. Twenty community health and education workers per site will be enrolled (total n=40) for training and postintervention assessment; this number reflects the total eligible cadre of ASHAs, ANMs, AWWs, and grade 8‐12 female teachers attached to the selected clusters at each site, and was not derived from a formal power calculation, consistent with standard practice for facilitator and trainer cohorts in implementation feasibility studies.

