### Phase 3: Intervention and Follow-up

A total of 416 adolescent girls aged 13‐19 years, equally divided between the 2 study sites, who complete the phase 2 sensitization and provide consent or assent for product use, will be allocated to either of the following:

MC group: receives a size-appropriate medical-grade silicone MC with instructional manual.MP group: receives 3 reusable MPs with instructional pamphlets.

Allocation to the MC or MP group will be based on participant preference following a structured counselling session in which both products, their insertion or use requirements, and maintenance needs are explained; girls who express no strong preference will be allocated using a randomization sequence generated in blocks of 4, stratified by site, to achieve approximately equal group sizes. This preference-informed allocation approach was chosen, rather than full randomization, because acceptability and correct use of MCs in particular are strongly influenced by willingness to use an internally inserted product, and forcing product allocation against strong preference was judged likely to compromise both retention and the validity of acceptability outcomes in a feasibility study of this nature; this deviation from a purely randomized design, and its rationale, is reported here transparently as recommended for feasibility study reporting [20].

Participants will receive free products along with instructional materials and menstrual-tracking diaries that record menstruation dates, school attendance, side effects, and usage challenges. Monthly follow-ups will occur through home visits at 1, 2, 3, 6, 9, and 12 months, conducted by trained community health and education workers using a structured follow-up checklist.

A 12-month follow-up duration was chosen in line with prior longitudinal descriptive work showing that adaptability and correct use of MCs typically stabilize only after several menstrual cycles of sustained use and support [25].

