### Data Analysis

Quantitative data will be analyzed using SPSS (v25). Descriptive statistics (frequencies, means, and SDs) will be used to summarize participant characteristics and uptake. Paired 2-tailed *t* tests and chi-square tests will evaluate pre- and postintervention differences in knowledge, attitude, and practice scores. Multivariate logistic regression will examine predictors of product adoption and continuation, including site, residence type (urban or rural), age, product type (MC vs MP), and baseline knowledge and attitude scores, with statistical significance set at *P*<.05. Qualitative data will be analyzed thematically using NVivo (v14), following the 6-phase reflexive thematic analysis approach described above.

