## Results

This protocol reports on a study that is funded and currently being implemented. The study was funded by the Indian Council of Medical Research in March 2024 (Proposal ID: IIRPSG-2024-01-03552). Ethics approval was granted by the Postgraduate Institute of Medical Education and Research Chandigarh Institutional Ethics Committee in January 2024 and by the AIIMS Kalyani Institutional Ethics Committee in April 2024.

Phase 1 stakeholder sensitization workshops were completed at both sites between July and September 2024. All 40 targeted community health and education workers (20 per site) were enrolled and completed training, giving a phase 1 retention rate of 100%. Pre-post assessment of this cohort showed an increase in mean knowledge scores following training; a full analysis of these phase 1 outcomes will be reported separately once phase 2 data collection is complete, consistent with journal guidance to avoid reporting substantive analytic results at the protocol stage.

Phase 2 adolescent sensitization commenced in October 2024. As of March 2026, 512 of the planned 912 (56%; n=268 in Kalyani and n=244 in Chandigarh-Panchkula) adolescent girls have completed baseline sensitization sessions. Of these, 210 of the planned 416 (51%) girls eligible for phase 3 have provided consent or assent and have been allocated to the MC (n=104) or MP (n=106) group; enrollment in the remaining clusters is scheduled to continue through 2026.

One deviation from the original grant proposal has occurred to date: the Chandigarh site catchment was expanded to include the district of Panchkula, Haryana, in addition to the originally proposed urban Chandigarh sectors, in order to incorporate a peri-urban or rural comparison population within the same site, as detailed in the Study Setting section above. This change was approved by both ethics committees as a minor protocol amendment prior to the start of phase 2 recruitment at that site.

Data collection for phase 3 follow-up is expected to continue through December 2026. Data analysis is planned for the first quarter of 2027, with submission of substantive outcome findings for peer-reviewed publication anticipated by late 2027.

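### The cohort is sized on product uptake, but uptake is not measured among the sensitized girls: phase 3 entry is capped and use within phase 3 is conditional on consent

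*Protocol article*

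**What the plan says.** Under Study Flow and Sample Size Calculation, the cohort is sized by "assuming a baseline sustainable-product usage rate of 5% and a projected postintervention uptake of 20" percent, "with 80% power and 5% significance". This gives 304 girls per site, then 456 per site and 912 in total after a design effect of 1.5. The same section adds that "a subgroup of 416 girls (n=208 per site) will be enrolled in the phase 3 product-use follow-up". It calls that size pragmatic and ties it to recruitment, retention and continuation.

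Phase 3: Intervention and Follow-up splits these girls equally between the sites and limits entry to those "who complete the phase 2 sensitization and provide consent or assent for product use". They receive the products free. Product usage and continuation are primary outcomes of this phase.

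In the wider cohort, the phase 2 section describes questionnaires on knowledge, attitudes and perceived readiness to adopt.

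Uptake nevertheless returns as a result. It is a joint-display domain under Mixed Methods Integration and a rural-urban contrast under Representativeness and Subgroup Considerations. Adoption rates are listed as a quantitative outcome in the Discussion. Under Data Analysis, "Multivariate logistic regression will examine predictors of product adoption and continuation, including site", with product type (cup or panty) among the other covariates.

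On progress, the Results section reports that "210 of the planned 416 (51%) girls eligible for phase 3 have provided consent or assent", set against 512 girls sensitized so far.

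**The concern.** Uptake after facilitator-led education is the quantity that justifies 912 girls, and its predictors are to be modelled. To estimate it, one needs to know which sensitized girls were offered a product and what each of them answered. The article describes neither. What it does record on product use comes from a phase 3 group that has a fixed target size, has equal numbers per site and was selected on willingness.

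At stake are the uptake figure, the site and residence contrasts on it, and the recruitment rate, which the sample size section itself names as a feasibility objective. If offers and refusals are not recorded at the time, an analyst cannot rebuild them later.

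**Working it through.** **1. The plan's own figures.** Inputs from the sample size section: 5% against 20%, 80% power, 5% significance (sidedness not stated).

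- Two-sided, pooled formula: n = [1.96·√(2·0.125·0.875) + 0.8416·√(0.05·0.95 + 0.20·0.80)]² / 0.15² = (0.917 + 0.383)² / 0.0225 ≈ 75.1, so 76 per group (88 with continuity correction).
- One-sided: 60 (72 with correction). Two-sided at 90% power: 101 (114 with correction).
- None of these gives the stated 304 per site. 304 = 4 × 76, so it may be a total over two groups and two sites; that is an assumption.
- The later steps reproduce. The design effect is 1 + 24 × 0.02 = 1.48, rounded to 1.5; 304 × 1.5 = 456; 2 × 456 = 912.

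The failure to reproduce 304 is a separate matter. What counts here is that 912 is derived from an uptake contrast.

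**2. What is measured, and in whom.**

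| Quantity | Sensitized cohort (912) | Phase 3 group (416) |
|---|---|---|
| Knowledge, attitudes, readiness | yes, pre and post | – |
| Offer of a product and response | not described | entry implies acceptance |
| Product use and continuation | not described | yes |

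**3. Reading A: adoption is phase 3 entry among all sensitized girls.** The largest observable share per site is 208/456 = 416/912 = 45.6%. With the other stated target it is 203/456 = 406/912 = 44.5%.

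The ceiling matters only if it is reached. The projected 20% is 0.20 × 456 = 91 girls per site, well below 208. Let X be the number accepting, X ~ Binomial(456, p). The expected observed share is E[min(X, 208)]/456.

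| True acceptance p | Expected observed share | Chance that a site fills |
|---|---|---|
| 20% | 20.0% | practically 0 |
| 30% | 30.0% | practically 0 |
| 40% | 40.0% | 0.9% |
| 45% | 44.3% | 41% |
| 50% | 45.6% | 97% |
| 60% | 45.6% | about 100% |

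This ignores clustering. Clustering would spread X more widely and make the change around 45% less sharp. True rates of 50% at one site and 70% at the other would both appear as about 45.6%.

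**4. Reading B: adoption is use within phase 3.** The product-type covariate points this way, since a girl outside phase 3 has no allocated product. Every girl in this denominator has already agreed to use a product and receives it free. The rate describes use given acceptance. It is not uptake among the girls who were sensitized.

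**5. Progress to March 2026.** 210/512 = 41.0% of sensitized girls have been allocated, about twice the projection and below the ceiling. The text does not divide the other 512 − 210 = 302 into declined, pending and not offered. The participant flow figure is not reproduced in the copy reviewed and may do so.

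**6. The target itself.** 416 in total or 208 per site appears in the sample size, phase 3 and Results sections. The Abstract has 406, and the sample size section also has 203 per site. The same 210 girls are therefore 52% of target in the Abstract (210/406) and 51% in the Results (210/416), each rounded as the article gives them.

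**The case against.** A reader might infer that the design fixes the adoption rate, that the trial cannot show a rise in uptake, and that equal targets force a site odds ratio of 1. The documents do not support this.

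- The ceiling binds only if about 45% or more accept. A rise from 5% to 20% would be seen in full.
- A filled target would itself show that at least 45.6% agreed to use a product. That is a lower bound well above 5%. The cap limits what can be seen of uptake; it does not create uptake.
- A crude site odds ratio of 1.00 needs both targets exactly filled and equal denominators. 456 is called a minimum, and the sites stand at 268 and 244.
- No rule for closing enrolment is stated, and nothing says that girls not offered a product are coded as refusers. A bias in residence type through the order in which clusters are visited is therefore conjecture.

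Three further points are fair. Objective 2 concerns awareness, knowledge and readiness, measured before and after the sessions and untouched by the phase 3 target. The subgroup analyses are labelled hypothesis-generating. An exact definition of adoption may be left to an analysis plan that is not shown. Data Analysis also mentions practice scores, and the full questionnaire sits in an appendix that is not shown, so an item on use may exist.

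All of this narrows the point without removing it. A definition written later cannot supply offers and refusals that were not recorded, and a product-type predictor of adoption is undefined for girls without a product.

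**Conclusion.** The concern holds in a limited form. As the article describes the study, neither natural reading of adoption reliably gives uptake among sensitized girls. Phase 3 entry is right-censored at 45.6% per site (44.5% with 203), and equals acceptance only if the target does not fill and every completer is offered a product, which is not stated. Use within phase 3 is conditional on consent and free supply.

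The censoring is harmless at the projected 20% and at 30%. It becomes material at a true acceptance of about 45%, and at 50% or more it hides both the size of uptake and differences between sites. The 41.0% allocated so far is close enough to make this a practical question, though that figure mixes girls who declined with any who are pending or not offered.

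This rests on two assumptions: that the phase 3 target acts as a maximum, and that the phase 2 questionnaires hold no measure of actual use beyond what the article describes. Because 912 − 512 = 400 girls remain to be sensitized, the gap can still be closed for a large part of the cohort.

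**What to change.** - Define uptake as acceptance of a product among phase 2 completers who were offered one.
- Record for every girl whether she was offered a product (if not, why) and her response: accepted the cup, accepted the panty, accepted with no preference, or declined with reason. Retrieve the same information for the 512 girls already seen, where records allow.
- Fit the adoption model in the offered denominator, without product type as a predictor. Report girls who were not offered a product separately.
- Do not interpret 416/912, or a site coefficient on it, as adoption.
- Report continuation as conditional on having accepted a free product.
- Reconcile 416 and 208 per site with 406 and 203 per site.

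The cost is one extra line on a form, a search of existing records and a revised outcome definition. Records for early clusters may be incomplete. Preference is elicited after structured counselling, so the response should be recorded at that point; girls who do not reach counselling are logged as not offered.

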**Methods:**

This is a mixed methods, 2-phase interventional feasibility study at 2 Indian sites (Kalyani, West Bengal, and Chandigarh and Panchkula, North India), chosen to represent contrasting urban-planned and mixed urban-rural catchments. Phase 1 trains 40 community health and education workers (accredited social health activists, auxiliary nurse midwives, Anganwadi workers, and female teachers), who then deliver structured education to 912 adolescent girls in phase 2. A subset of 406 girls will be allocated to MCs or MPs and followed for 12 months via diaries, home visits, and focus group discussions. Quantitative data will be analyzed in SPSS; qualitative data will undergo reflexive thematic analysis in NVivo, guided by the Behavior Change Wheel and Capability, Opportunity, Motivation–Behavior framework. A cost-utility analysis using EQ-5D-Y and quality-adjusted life-years will assess cost-effectiveness from a societal perspective.

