**Results:**

The study is funded by the Indian Council of Medical Research (proposal IIRPSG-2024-01-03552), with funding confirmed in March 2024. Ethics approval was obtained in January 2024 (Postgraduate Institute of Medical Education and Research, Chandigarh) and in April 2024 (All India Institute of Medical Sciences, Kalyani). Phase 1 sensitization was completed at both sites by September 2024, with all 40 workers trained (retention 100%). As of March 2026, 512 of 912 (56%) adolescent girls have completed phase 2 sensitization, and 210 of 406 (52%) have been enrolled and allocated to MCs or MPs in phase 3. Data collection is expected to conclude by December 2026, with analysis in early 2027 and outcome findings to be submitted for publication by late 2027.

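### Phase 3 target is stated as both 416 (208 per site) and 406 (203 per site); the accompanying ±16% precision threshold does not hold at a proportion of 50%

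*Protocol article*

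**What the plan says.** Two targets for the phase 3 product-use cohort appear in the current text of the protocol article.

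- **416:** Study Flow and Sample Size Calculation, "a subgroup of 416 girls (n=208 per site) will be enrolled in the phase 3 product-use follow-up"; Phase 3: Intervention and Follow-up, "A total of 416 adolescent girls aged"; main Results, "210 of the planned 416 (51%) girls eligible for phase 3".
- **406:** Abstract, Methods, "A subset of 406 girls will be allocated to MCs or MPs and followed for 12 months"; Abstract, Results, "210 of 406 (52%) have been enrolled and allocated to MCs or MPs in phase 3"; and, in the same sample size paragraph that gives 416, "the planned 203 girls per site substantially exceeds this threshold".

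That paragraph describes the phase 3 size as pragmatic and justified by recruitment, retention and product continuation. It then says that 30 to 35 participants in each arm at each site are "adequate to estimate continuation and acceptability proportions with reasonable precision (95% CI width ≤±16%) for feasibility purposes". It gives no expected proportion, interval method or clustering allowance for that statement. The design effect of 1.5 in the same paragraph (ICC 0.02, 25 girls per cluster) is stated for the phase 2 cohort.

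**The concern.** A trial should have one target. Here recruitment is itself a primary feasibility objective, so the target is the denominator of a result, and the article already reports that result in two ways. Enrolment is still open, so the number is also in operational use. Neither figure is marked as superseded: the only deviation that the Results section reports is the extension of the Chandigarh catchment.

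The precision sentence is the only quantitative support offered for the phase 3 size. Read with the usual conservative proportion of 50%, the threshold does not deliver the stated half-width. The sentence also sets a threshold defined per arm and per site against a per-site total over both arms.

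**Working it through.** **1. Target and percentages**

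Inputs: 208 and 203 per site, two sites, 210 girls allocated.

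- 2 × 208 = 416; 2 × 203 = 406; difference 10 girls (10/416 = 2.4%).
- 210/406 = 51.7%, printed as 52% in the abstract: correct.
- 210/416 = 50.48%, printed as 51% in the main Results: it rounds to 50%.

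Each total has its own matching per-site figure, so a single mistyped digit does not explain the conflict.

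**2. The ±16% threshold**

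The stated width is read as a half-width because of the ± sign. Formula (Wald): h = 1.96 × √(p(1−p)/n). With p not given, p = 0.5 is the standard conservative choice.

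- n = 30: 1.96 × √(0.25/30) = 0.179
- n = 35: 1.96 × √(0.25/35) = 0.166
- n for h = 0.16: (1.96 × 0.5/0.16)² = 37.5, so 38

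Other methods at p = 0.5, without clustering:

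| Method | n = 30 | n = 35 |
|---|---|---|
| Wald | ±17.9% | ±16.6% |
| Wilson | ±16.9% | ±15.7% |
| Exact | about ±18.7% | about ±17.3% |

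No 95% method tried reproduces ±16% over the whole range from 30 to 35 at p = 0.5; Wilson reaches it only from n = 34.

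Proportions for which the Wald half-width does meet ±16%, from p(1−p) ≤ n × (0.16/1.96)²:

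- n = 30: p(1−p) ≤ 0.200, so p ≤ 0.276 or p ≥ 0.724
- n = 35: p(1−p) ≤ 0.233, so p ≤ 0.371 or p ≥ 0.629

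**3. Precision at the planned size**

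With roughly equal arms, 203/2 to 208/2 gives about 101 to 104 per arm per site. At p = 0.5:

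- No clustering: 1.96 × √(0.25/101) = 0.098; 1.96 × √(0.25/104) = 0.096.
- Phase 3 girls spread evenly over the phase 2 clusters (an assumption): 456/25 is about 18 clusters per site. Then 203 to 208 girls are about 11 per cluster, or 5 to 6 per arm. Design effect about 1 + (5.7 − 1) × 0.02 = 1.09. Half-width 0.098 × √1.09 = 0.102 to 0.096 × √1.09 = 0.100.
- Full design effect of 1.5 as an upper bound: 0.0975 × √1.5 = 0.119; 0.0961 × √1.5 = 0.118.

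All are before attrition.

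**The case against.** The strongest reply is that the precision sentence is harmless. It sets a minimum, states no proportion, and holds at n = 35 for a continuation proportion of about 63% or more, at n = 30 for about 72% or more, and for equally low proportions. The planned arms are about three times the minimum, so the plan's conclusion that the threshold is well exceeded stays true when the comparison is made per arm. Allocation so far (104 to cups, 106 to panties) supports roughly equal arms, although preference-based allocation does not guarantee them. The phase 3 size is also called pragmatic and does not depend on this sentence. All of this stands, and it makes the precision point secondary.

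A reader might go further and infer that the plan overstates its precision or that phase 3 is too small. The documents do not support that: ±16% is attached to the 30-35 minimum, and the planned size does better. Nor do they support a required 57 per arm per site (38 × 1.5). That carries over a design effect derived for 25 girls per cluster, and the documents do not say that a phase 3 arm would have that many in each cluster.

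Nothing in the reply touches the conflict between 416 and 406.

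**Conclusion.** The phase 3 target is inconsistent by 10 girls, and nothing in the article shows which figure is intended. This rests on reading alone. The enrolment percentage differs accordingly (51.7% or 50.5%), and the printed 51% matches neither denominator after rounding.

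The threshold of 30-35 per arm per site is misstated at a proportion of 50%, by 0.6 to 1.9 percentage points with a Wald interval; 38 would be needed without clustering. It is not wrong for every proportion, and the omission is that none is stated. The planned sample meets ±16% with room to spare: about ±10% if clusters contribute evenly, and at most about ±12% under the full design effect. That conclusion assumes roughly equal arms and no attrition. The consequence is for reporting and documentation; it does not call the size of the study into question.

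**What to change.** State one phase 3 total with its per-site figure in the abstract, the sample size paragraph, the Phase 3 section and the main Results, and compute the enrolment percentage from it: 52% if the target is 406, 50% if it is 416. The sponsor must say which target is intended.

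Delete the 30-35 sentence and give the precision at the planned size, naming proportion, method and clustering assumption. For example: about 101-104 girls per arm per site, if arms are roughly equal, give a 95% Wald half-width at 50% of about ±9.6% to ±9.8% without clustering, about ±10% with an ICC of 0.02 and even spread over the phase 2 clusters, and at most about ±12% with a design effect of 1.5, before attrition. If a minimum is kept, state its assumed proportion and express it and the planned number on the same per-arm, per-site basis.

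The cost is a text correction. The design and the planned analysis do not change.
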